#### Sub-group analyses

Subgroup analyses will be carried out to explore the impact of number of medications, age, HbA1c, self-reported adherence at baseline and prior randomisation to the electronic medication-monitoring device on the intervention effect.

#### Additional analyses

We will assess the impact of the intervention on beliefs about taking diabetes medication, and test whether any observed change in medication adherence is mediated by the intervention's impact on beliefs. We will explore the potential role of nurse communication style as a moderator of effect. We will compare the differences between participating and non-participating patients.

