## Methods/Design

### Trial design

This parallel group trial has two sequential randomisations. The main randomisation takes place eight weeks after recruitment, is unbalanced and compares a two-component intervention addressing motivation and action planning with a control intervention in which patients only take part in data collection (Figure 1). Unbalanced randomisation is used to maximise experience with the intervention across a range of patients with follow up at twenty weeks. The measurement effect randomisation, which takes place at the baseline recruitment visit, is balanced and assesses the effect of dispensing medication in a container that records opening compared with dispensing medication in standard packaging: with follow up at eight weeks.

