### Study procedures

#### Baseline data collection and randomisation to electronic medication taking measurement

Eligible patients registered with the practice are identified by the practice nurse. Baseline data from the notes is recorded by the practice nurse and anonymised to provide data from which to characterise the population from which participants were recruited. Eligible patients are sent a letter from the practice including study details, a questionnaire asking about basic demographics, medication regimen, self-reported medication adherence, and beliefs about taking diabetes medicines without missing a day (Table 1 and Table 2). If willing to help further, a phone call is made by the practice nurse to the patient to arrange a study appointment.

**Table 1 T1:** Trial measures and timing

	Baseline visit	Before 8 week visit	At 8 week visit	After 8 week visit	Final visit at 20-weeks
Basic demographics	x				

Medication	x		x		x
Co-morbidity	x				

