**Psychological**					
TPB† Direct measures and intention	x	x		x	
TPB† Indirect measures	x	x		x	
Time and location of taking medicines					x
Communication with practice nurse					x

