### Measurement

#### Primary outcome for intervention trial

The primary outcome for the intervention is the percentage of days on which the prescribed dose of main hypoglycaemic medication is taken as prescribed, measured with the TrackCap electronic medication monitor over a 12-week period from eight to twenty weeks.

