#### Psychological and process measures

A questionnaire based on the Theory of Planned Behaviour is used to assess attitude, subjective norm, perceived behavioural control, and intention to take diabetes medicines without missing a day. The questionnaire also assesses perceived consequences of taking diabetes medication (behavioural beliefs); perceived views of significant others about taking diabetes medication (normative beliefs); perceived factors that make taking diabetes medication easier or difficult (control beliefs). These measures are based on our earlier pilot work [19].

We are using a measure to assess patients' ratings of communication with nurses (covering the ability to tell the nurse personal or troubling things and feeling understood) [25], and ask open-ended questions about when and where medications are usually taken. Tape recordings of consultations are used to assess fidelity of intervention delivery, using a-priori criteria. The intervention facilitators record adherence to techniques specified in the intervention script on standardised forms.

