## Discussion

This trial is designed to estimate the efficacy of a two-component intervention targeting determinants of intentions and action planning as possible mediators of improved medication adherence. Measures and interventions have been developed using the approach defined by the Medical Research Council Framework for development of interventions for evaluation in randomised trials [20,21]. In addition to estimating efficacy the trial will provide information on psychological mechanisms of increasing medication adherence and assess the impact of trial measurement on outcomes.

We are conducting this trial in a well characterised primary care population. The training of nurses to deliver the intervention uses scripts and feedback from taped intervention sessions to maximise delivery as planned and consistent delivery across nurses and over time. We are able to test impact of the communication style of the practice nurse by examining the relationship between patient attitudes about communication and behavioural outcomes. We have optimised clear communication of the intervention through training and feedback to the nurses delivering the intervention.

This trial has been designed to address the weaknesses of previous work in the area of medication adherence. It approaches medication taking as a discrete behaviour and uses psychological theory and evidence in the design of intervention to address intentions and the step from intention to actions, and in measurement of the process. It will therefore be possible to explore the extent to which interventions that address these components of medication adherence might improve outcomes. Additional analyses will estimate the extent to which any observed effects of the intervention on behaviour are mediated by intention and action planning. The trial will explore the extent to which previous trials may have failed to show efficacy as a result of the kind of people who participate in such trials, and the kinds of measures of adherence used, including the impact of measurement itself on adherence and HbA1c.

This trial will provide one of the first evaluations of an intervention developed using psychological theory to support patients in adherence to diabetes medication. If the trial provides evidence of efficacy, it will add to the clinical approaches for medicines education currently in use.

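### Nurse communication is to be explored as a moderator, but it is rated only at 20 weeks, after the intervention visit and the whole outcome period, so an interaction with it would not identify effect modification

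*Protocol article*

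**What the plan says.** - **Planned analysis.** Under Additional analyses: "We will explore the potential role of nurse communication style as a moderator of effect".
- **Instrument.** Under Psychological and process measures: "We are using a measure to assess patients' ratings of communication with nurses". It covers how far patients can confide in the nurse and feel understood. The Discussion confirms that this rating is the instrument, since communication style is to be tested "by examining the relationship between patient attitudes about communication and behavioural outcomes".
- **Timing of the rating.** In Table 1 the row "Communication with practice nurse" has one mark, in the last column, "Final visit at 20-weeks". Nothing is marked at baseline or before, at or just after the 8-week visit.
- **Timing of treatment and outcome.** Under Trial design: "The main randomisation takes place eight weeks after recruitment, is unbalanced". The primary outcome is "measured with the TrackCap electronic medication monitor over a 12-week period from eight to twenty weeks".
- **Nurse contact.** Under Intervention and control visit, the intervention interview lasts 50 minutes and the control visit about 20.

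**The concern.** A moderator has to be fixed before treatment, or at least be unaffected by it. Otherwise the interaction mixes how the effect varies between patients with how treatment and outcome shaped the supposed moderator.

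Both routes are open here. A long conversation that draws out a patient's beliefs may change whether that patient feels understood, so arm can move the rating. Twelve weeks of adherence going well or badly may colour a rating given at the end, so outcome can move it too. If the second influence differs between arms, an interaction appears where no moderation exists.

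At stake is a conclusion that the intervention works better with nurses who communicate well, when patients who did well may simply have rated their nurse more kindly. The article fixes both the moderator role and the measurement time, and an analysis plan cannot supply a pre-intervention rating that was never collected.

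**Working it through.** **1. Order of events in the article**

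| Week | Event |
|---|---|
| 0 | Baseline visit of 40 minutes with the practice nurse; communication not rated |
| Before the week-8 visit | Questionnaire completed at home; communication not rated |
| 8 | Main allocation, made ahead of the visit; then 50 or about 20 minutes with the nurse |
| 8 to 20 | Primary outcome period |
| 20 | Communication rated for the only time |

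No other source of an arm-independent rating appears. The audiotapes assessed under Intervention fidelity are of intervention sessions and serve fidelity scoring. The factors under Sub-group analyses do not include communication.

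**2. Inputs**

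The plan gives no figure to reproduce on this point. From the article: 200 patients followed up; 3:2 allocation, so 200 × 3/5 = 120 and 200 × 2/5 = 80; effect 5 percentage points; SD 13.5. The standardised effect is 5/13.5 = 0.37. The correlations and the 0.5 SD shift in the rating are assumptions, because the article gives neither.

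**3. False-positive rate of the interaction test**

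Model with no true moderation: Y = 5·T + 13.5·e, and R = shift·T + r(arm)·(outcome) + noise. Fit Y on T, R and T×R, and test T×R at two-sided 5%, with at least 4,000 simulated trials per setting.

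| Rating-outcome correlation, control / intervention | Rejection rate |
|---|---|
| 0 / 0 | about 5% |
| Equal, 0.2 to 0.4 in both | about 5% |
| 0.1 / 0.2, 0.2 / 0.3, 0.3 / 0.4 | about 11% |
| 0 / 0.1 | 10% |
| 0 / 0.2, 0.1 / 0.3 | about 28% |
| 0 / 0.3 | 56% |

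The rate is driven by the difference in correlation between arms. A shift in the rating by arm with no correlation leaves it at about 5%.

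**4. Treatment coefficient after adjustment for the rating**

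Suppose a shared patient trait gives the same correlation r in both arms and the intervention raises the rating by 0.5 SD. The adjusted coefficient at the mean rating is then 13.5 × (0.37 − 0.5·r):

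- r = 0.2: 13.5 × 0.27 = 3.6 (simulated 3.7)
- r = 0.3: 13.5 × 0.22 = 3.0 (simulated 3.0)
- r = 0.4: 13.5 × 0.17 = 2.3 (simulated 2.3)

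Without the shift the formula returns 13.5 × 0.37 = 5, and simulation agrees (4.96 to 5.04). If the rating instead follows the outcome itself, the treatment effect is carried into the rating as well. With r = 0.3 and the 0.5 SD shift, the coefficient is 5 − 13.5 × 0.3 × (0.5 + 0.3 × 0.37) = 2.5 (simulated 2.55).

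**5. Check of the remedy**

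With a rating that depends on neither arm nor outcome, as a pre-intervention score should be, the test rejects in 5.2% of trials and the treatment coefficient is 4.99.

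**The case against.** **The higher rates depend on an arm difference that nothing in the article establishes.** A reader might infer that the planned test will mislead in a quarter to a half of trials. The documents do not support that. Control patients also see practice nurses at baseline, 8 weeks and 20 weeks, so a contented or adherent patient may rate the nurse well in either arm. Equal correlations keep the test at its nominal level. This objection stands: the result is a range that starts at 5%. Unequal nurse contact makes some difference between arms plausible, but its size is unknown.

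**A shared trait alone does not shrink the effect.** A reader might infer that any link between rating and adherence biases the treatment coefficient towards zero. In the shared-trait case the shrinkage comes wholly from adding the assumed 0.5 SD shift. It is also bias in an adjusted coefficient, not false moderation.

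**The stakes are low.** The analysis is exploratory and listed under Additional analyses, and the article specifies no model, so the interaction regression above is one reasonable reading. The primary analysis compares randomised means by bootstrap and does not condition on the rating. A reader might infer a threat to the efficacy result; there is none.

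**Part of the Discussion describes only an association.** The phrase "examining the relationship between patient attitudes about communication and behavioural outcomes" is accurate as such. However, the same sentence offers this as a test of the impact of communication style, and the analysis section uses the word moderator. A 20-week rating does not support either.

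The timing itself is not in dispute. The table was read from a PDF, but the position of the mark fits the neighbouring rows.

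**Conclusion.** The point holds in a limited form. The only rating of communication is taken after allocation, after unequal nurse contact and after the complete outcome period, so an arm-by-rating interaction cannot be read as effect modification.

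How far it would mislead depends on unknown correlations: about 5% false positives if they are equal in the two arms, about 11% for a difference of 0.1, about 28% for 0.2, and 56% for 0 against 0.3. An adjusted treatment coefficient would fall from 5 to about 3.7 to 2.3 points with correlations of 0.2 to 0.4 in both arms, provided the intervention also raises the rating by 0.5 SD. All of these rest on assumed values.

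The issue is minor to moderate. It touches one exploratory analysis and the claim made for it in the Discussion.

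**What to change.** 1. Add the existing communication scale to the baseline questionnaire, which certainly precedes the main randomisation, or to the one already completed before the 8-week visit. The second option lets patients rate the nurse after the 40-minute baseline visit, but the article does not say whether allocation or that questionnaire comes first. If it is used, the order should be stated.
2. Use that score as the moderator.
3. Keep the 20-week rating as a process outcome compared between arms. Where no pre-intervention score exists, report its relation to adherence as an association, and reword the Discussion to match.
4. A nurse-level score from control patients is only a fallback. About 80 controls would be spread over an unstated number of nurses, so its reliability is uncertain.

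**Cost.** A slightly longer form and a minor amendment to an ethics-approved protocol. Patients already past week 8 will have no pre-visit score. The new score also reflects communication before the intervention visit, not how the nurse communicated while delivering it.

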## Discussion

This trial is designed to estimate the efficacy of a two-component intervention targeting determinants of intentions and action planning as possible mediators of improved medication adherence. Measures and interventions have been developed using the approach defined by the Medical Research Council Framework for development of interventions for evaluation in randomised trials [20,21]. In addition to estimating efficacy the trial will provide information on psychological mechanisms of increasing medication adherence and assess the impact of trial measurement on outcomes.

We are conducting this trial in a well characterised primary care population. The training of nurses to deliver the intervention uses scripts and feedback from taped intervention sessions to maximise delivery as planned and consistent delivery across nurses and over time. We are able to test impact of the communication style of the practice nurse by examining the relationship between patient attitudes about communication and behavioural outcomes. We have optimised clear communication of the intervention through training and feedback to the nurses delivering the intervention.

This trial has been designed to address the weaknesses of previous work in the area of medication adherence. It approaches medication taking as a discrete behaviour and uses psychological theory and evidence in the design of intervention to address intentions and the step from intention to actions, and in measurement of the process. It will therefore be possible to explore the extent to which interventions that address these components of medication adherence might improve outcomes. Additional analyses will estimate the extent to which any observed effects of the intervention on behaviour are mediated by intention and action planning. The trial will explore the extent to which previous trials may have failed to show efficacy as a result of the kind of people who participate in such trials, and the kinds of measures of adherence used, including the impact of measurement itself on adherence and HbA1c.

This trial will provide one of the first evaluations of an intervention developed using psychological theory to support patients in adherence to diabetes medication. If the trial provides evidence of efficacy, it will add to the clinical approaches for medicines education currently in use.

If the two-component intervention shows evidence of efficacy, we propose to compare it with the action-planning only intervention in a future trial. Future research in this area will also need to incorporate detailed health economic assessments to assess cost-effectiveness. However, because of the large numbers of people with diabetes, even very small effects of an intervention on adherence offer potential for major public health gains.

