#### Intervention and control visit

Prior to the eight-week study visit patients are sent a questionnaire to be completed at home and returned to the coordinating centre in a sealed envelope by post. At the eight-week visit, patients allocated to the intervention take part in a 50 minutes interview with the practice nurse including the intervention and data collection. The control visit lasts approximately 20 minutes in which the data are collected. All patients at the eight week visit have blood samples taken and inquiry made about any possible adverse events including hypoglycaemia. A postal questionnaire is completed one week after the eight week visit.

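### The Discussion promises an estimate of mediation by action planning, but the measurement schedule holds no planning measure before or during the outcome window, so the claim should be limited to intention and beliefs

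*Protocol article*

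**What the plan says.** Three parts of the protocol article bear on this point.

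- **The promise.** The Discussion says: "Additional analyses will estimate the extent to which any observed effects of the intervention on behaviour are mediated by intention and action planning". Two mediators are named, one for each component of the intervention.
- **The planned analysis.** Under Analysis, the Additional analyses section says the trial will "test whether any observed change in medication adherence is mediated by the intervention's impact on beliefs". Action planning does not appear there.
- **The measurements.** In the psychological block of Table 1, the only entry close to planning is "Time and location of taking medicines". It is marked in one column, "Final visit at 20-weeks". The section on psychological and process measures describes it only as a plan to "ask open-ended questions about when and where medications are usually taken". The Theory of Planned Behaviour items are marked at baseline, before the 8-week visit and after it. On the last of these, the section on the intervention and control visit says: "A postal questionnaire is completed one week after the eight week visit".

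The primary outcome is electronically monitored adherence "over a 12-week period from eight to twenty weeks".

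**The concern.** To interpret an indirect effect, the mediator should be measured in both arms, after the intervention and before the outcome (or at least early in it), preferably with a pre-intervention value to adjust for. Intention and beliefs come close to this. Action planning does not, because nothing in the schedule records it in both arms until the outcome window has closed.

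If the 20-week answers were used to fill the gap, the direction of influence would be open. A patient who has taken tablets regularly for 12 weeks is likely to describe a settled time and place, whether or not a plan produced the regularity. A fitted indirect effect could then be reported as evidence on the volitional component when it reflects the outcome itself. What is at stake is one stated explanatory output of the trial, not its efficacy result.

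**Working it through.** The article gives no figure to reproduce here. The check compares the promise with the schedule, then uses a simple calculation to show how far reverse influence could mislead.

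**1. Candidate measures of action planning**

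| Candidate | Where described | Both arms? | When recorded | Usable as a mediator? |
|---|---|---|---|---|
| Theory of Planned Behaviour items | Table 1, Table 2 | Yes | Baseline, before the 8-week visit, about week 9 | For intention and beliefs. Table 2 lists attitude, norms, perceived control and intention, with no planning construct |
| Written if-then plan | Intervention section | No, intervention arm only | Week 8 | No. It is part of the intervention, is not listed as a measure and has no control counterpart |
| Tape recordings | Psychological and process measures | Not relevant | At the consultation | No. They assess fidelity of delivery, not the patient's planning |
| Time and location of taking medicines | Table 1, Psychological and process measures | Yes | Week 20 only | No. First recorded as the outcome window closes, with no earlier value |

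**2. Timing against the outcome window of 20 − 8 = 12 weeks**

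- Intention and beliefs: two values before the intervention and one at about week 9. The overlap with the outcome is 9 − 8 = 1 week, or 1/12 ≈ 8% of the window.
- Time-and-location item: one value, at week 20, and none before.

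**3. What reverse influence alone could produce**

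Suppose the intervention raises adherence Y by 5 points with an SD of 13.5 (both figures from the Sample size section), and that none of this runs through the 20-week item M. Let M simply reflect the adherence already achieved, with within-arm correlation r and M scaled to a within-arm SD of 1:

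- effect of arm on M: a = r × 5 / 13.5
- slope of Y on M within arm: b = 13.5 × r
- apparent indirect effect: a × b = 5r²
- apparent proportion mediated: 5r² / 5 = r²

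The last line does not depend on the 5 or the 13.5.

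| Assumed r | Apparent indirect effect (points of 5) | r² | Simulated, 3:2 allocation, 400,000 patients |
|---|---|---|---|
| 0.2 | 0.20 | 4% | 3.9% |
| 0.3 | 0.45 | 9% | 8.9% |
| 0.5 | 1.25 | 25% | 24.6% |
| 0.7 | 2.45 | 49% | 48.9% |

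The true proportion mediated is zero in every row. The correlations are assumptions, because the article gives none, so the table shows a range of possible error and not an estimate for this trial.

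**The case against.** The strongest reply has four parts.

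- **The article is condensed.** It never calls the time-and-location questions a planning measure, and the full questionnaires and analysis plan are not shown. It is therefore fair not to treat that item as the intended mediator. But Table 1 sets out the trial's measures and their timing, and an analysis plan cannot supply a measurement that was not taken. If the item is not the planning measure, the article names none, and the promise has less support still.
- **The item asks about usual practice.** The date of recording is not the period described, so the fact that all 12 outcome weeks come before the answer does not measure the bias. That is correct. It remains true that the answer is given after the outcome, may be shaped by it, and has no earlier value to adjust for.
- **Mediation is a minor aim.** It is an additional analysis; the aims at the end of the Background are efficacy and the measurement effect. This stands and limits the weight of the point.
- **Asking only at the end may be prudent.** Asking controls when and where they take their tablets resembles the action-planning component, and the trial is itself concerned that measurement changes behaviour. The article does not give this reason, but the argument stands and decides the form of the fix.

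A reader might also infer three stronger conclusions that the document does not support.

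- *The mechanism work as a whole fails.* It does not: intention and beliefs are measured before the 8-week visit and about one week after it.
- *The week-9 questionnaire is mistimed.* A mediator of an intervention given at week 8 has to be measured after week 8, and an overlap of about 1 week in 12 is minor.
- *The proposed next trial builds on this mediation result.* The Discussion makes that trial conditional on evidence of efficacy, and its randomised comparison with action planning alone would itself inform on the components.

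**Conclusion.** The point holds for action planning only. The Discussion claims an estimate that the stated schedule cannot deliver in interpretable form, and the claim does not match the Additional analyses section. A coefficient through the 20-week item can be computed, but mediation cannot be separated from the influence of adherence on the answers. Under the assumed correlations, reverse influence alone would appear as about 4% to 49% mediated.

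The conclusion rests on Table 1 being the complete schedule of measures, as its title indicates, and on the written plan having no counterpart in the control arm, as the Intervention section states. The primary outcome, its analysis, the sample size and the randomisation are unaffected. This is a modest correction to a stated capability, not a flaw in the main comparison.

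**What to change.** 1. In the Discussion, limit the mediation statement to intention and beliefs, and word the Additional analyses section to match. Action planning can remain a hypothesised mechanism, provided the text does not say that mediation through it will be estimated. Cost: one or two sentences.
2. Report the 20-week time-and-location responses by arm as descriptive or exploratory, and state that they will not be used as a mediator. Cost: none.
3. Optionally, in the intention and belief mediation models, add a sensitivity analysis that uses monitored adherence from the date of the one-week questionnaire onward, so that the mediator precedes the outcome. The monitor records the timing of each opening, so no new data are needed. Cost: about 1 of 12 weeks of outcome data in that analysis.

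Do not add time-and-location questions for controls around week 8. They would supply the missing values, but could prompt planning in controls just before and inside the primary outcome window and so dilute the primary contrast for the sake of an additional analysis.
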